#### Intervention

We will conduct an RCT with random assignment to one of three groups: (1) text messaging, (2) mobile app, or (3) website-control, for a total of 12 months. Both intervention groups will also be offered the patient education website that the control group will be given. The *text messaging group* will receive text messages with content and frequency informed by Aim 1. We will use the Veterans Affairs (VA) *Annie* text messaging program. For non-Veteran females, we will use a text messaging program from CareSpeak Communications. The *app group* will use the preferred app that is selected in Aim 2. The major purpose of the app is to remind participants to take medications; however, the app will likely include other features such as providing educational messages. The *website group* will be offered the American Heart Association patient education website (My Life Check - 7 Steps To Healthy Living) and will serve as an active control group [43]. The website will be offered to participants in all three groups. The *7 small steps to big changes* are to manage blood pressure, control cholesterol, reduce blood sugar, get active, eat better, lose weight, and stop smoking.

#### Follow-Up Visits

Subsequent in-person follow-up visits at 1, 6, and 12 months will take place in participants’ homes or other mutual meeting places as requested. Follow-up visits will be scheduled at times that are convenient for participants to meet.

### Primary Outcome/Other Variables and Instruments

#### Primary Outcome: Medication Adherence

Medication adherence will be assessed with five different measures at various intervals to validate patterns of adherence, including: Medication Event Monitoring System (MEMS; key primary endpoint being percentage of prescribed doses taken), Morisky Medication Adherence Scale (MMAS-8), 7-day recall, VA Corporate Data Warehouse (Veterans), and Peoplechart Meds Incontext (non-Veterans; Table 2). In-person follow-up visits will occur at 1, 6, and 12 months, while monitoring of adherence through refill data from computer software will be done monthly to reduce participant burden.

MEMS technology uses integrated microcircuits with bottle caps that record the date and time that an individual opens a pill bottle. Participants will be given one bottle to store their antiplatelet medication, and will be directed to store their other medications as they normally would. For those who use 7-day pill boxes, we will emphasize the need to use the MEMS bottle for the antiplatelet medication. Data will be wirelessly transferred to a MEMSCap reader, which is a small device that connects to a computer software program.

Refill data from computer software will also allow us to monitor prescription adherence passively, without requiring patient participation. We will use administrative data from the national VA repository (VA Corporate Data Warehouse) to provide adherence to antiplatelet medication for Veterans. For non-Veteran females from JMMC, we will use an equivalent data source through Peoplechart Meds Incontext, which is a software program that tracks adherence through sanctioned prescription data sourced directly from retail pharmacies and Prescription Benefits Managers (ie, mail-order companies).

#### Other Variables and Instruments

We will examine other variables (health-related quality of life, social support, self-efficacy, depression, anxiety, and post-traumatic stress disorder) and their relationship to medication adherence. Patients will complete the instruments at baseline, 1, 6, and 12 months (Table 3).

**Table 3 table3:** Instruments used to assess additional variables.

Measure	Description	Months					
		0	1	3	6	9	12
Health-related quality of life	The 12-Item Short Form Health Survey (SF-12) is the shorter version of SF-36, which measures functional health and well-being (relative validity median 0.67 and 0.97 for the physical and mental components, respectively) [44].	x	x		x		x
Social support	The 20-item Medical Outcomes Study Social Support Survey Instrument uses multi-trait scaling analyses of 4 functional support scales and provides an overall functional social support index (Cronbach alpha=0.91) [45].	x	x		x		x
Medication self-efficacy	The 13-item Self-Efficacy for Appropriate Medication Use Scale measures how confident individuals are in taking their medications correctly in certain situations (Cronbach alpha=0.89) [46].	x	x		x		x
Depression	The 9-item Patient Health Questionnaire is used to diagnose and measure the severity of depression as well as monitor response to treatment (Cronbach alpha=0.89) [47].	x	x		x		x
Anxiety	The 7-item Generalized Anxiety Disorder Assessment is used to screen and measure severity of generalized anxiety disorder (Cronbach alpha=0.92) [48].	x	x		x		x
Post-traumatic stress disorder	The 17-item Post-Traumatic Stress Disorder Checklist: Civilian is a popular self-report rating scale for post-traumatic stress disorder. The civilian version will be used instead of the military version because the majority of participants will not have been on recent active duty, >35% of Veterans with post-traumatic stress disorder had a nonmilitary trauma, and non-Veteran women will be included (29%; Cronbach alpha=0.87) [49].	x	x		x		x

#### Process Evaluation

Upon completion of the intervention study, we will conduct a process evaluation so that improvements can be made for a multi-site full scale study. The objectives of the process evaluation are to assess participants’ perspectives on feasibility, acceptability, usability, challenges, strengths, and weaknesses of the intervention. In addition, we will ascertain reasons for nonadherence to antiplatelet medications since understanding the reasons for nonadherence is crucial to avoid negative patient outcomes. We will adopt a qualitative research approach using in-depth individual interviews from a diverse sample of participants (total n=20).

#### Analysis

Descriptive statistics, means, and SDs for quantitative variables, and frequencies and percentages for categorical variables, will be provided for all demographic and study variables. Random assignment of the patients to the text messaging, mobile app, and website groups should ensure that there are no preexisting differences between the three groups in personal factors (eg, sociodemographic, clinical, and psychosocial characteristics).

#### Medication Adherence

The primary outcome will be the percentage of prescribed doses taken based on MEMS data (aggregated over 12 months). Secondary outcomes will include: (1) percentages of days correct number of doses were taken, (2) doses taken on schedule, (3) MMAS-8, (4) 7-day recall, (5) VA Corporate Data Warehouse (Veterans), and (6) Peoplechart Meds Incontext (non-Veterans). The MMAS-8 will be analyzed as a range of 0-8. We will synthesize adherence measures with the key primary endpoint of MEMS data compared with secondary measures of adherence to assess for concurrent and predictive validity. We will also calculate associations between all of the adherence measures but expect that they will track well together. Prior to fitting the mixed-effects linear model, we will examine univariate and bivariate relationships between the outcomes and both demographic and coded qualitative responses.

#### Primary Statistical Analysis

Our primary analysis will use a mixed-effects linear model. The predictors will be a categorical predictor of group (with control as reference), time, and the group-by-time interactions, as well as the recruitment site (SFVAMC vs JMMC), as randomization is stratified by site. The parameters in the group-by-time interaction are the primary parameters of interest, describing whether adherence changes differentially over baseline in each of the treatment groups compared to the control group. We will also investigate whether other models for change over time are more appropriate, including arbitrary means or nonlinear time functions through comparison of Akaike information criterion/Bayesian information criterion. Secondary analyses will adjust for select covariates that are strongly associated with adherence.

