### Preliminary Studies

In a pilot randomized controlled trial (RCT) from 2012-2013, we compared antiplatelet and statin adherence among patients with coronary heart disease in a 30-day study who received: (1) text messaging for medication reminders and education, (2) educational text messaging only, or (3) no text messaging [33]. Among 90 patients (76% male, mean age 59.2 years), electronic devices revealed that patients who received text messaging for antiplatelets had a higher percentage of correct doses taken (*P*=0.02), percentage number of doses taken (*P*=0.01), and percentage of prescribed doses taken on schedule (*P*=0.01) [33]. Text messaging response rates were higher for antiplatelets than statins (*P*=0.005), and self-reported adherence revealed no significant differences among groups [33]. We concluded that the use of text messaging for the medication reminders/education and education text messaging only groups (compared to no text messaging for the control group) increased adherence to antiplatelet therapy by 15% to 17%, respectively. We established feasibility and high satisfaction and concluded that mHealth interventions show promise in promoting medication adherence.

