#### Sample

The convenience sample will consist of 159 male and female Veterans from SFVAMC and 66 female participants (29% of sample) from JMMC. A sample size of 225 is considered to be feasible considering the number of post-ACS/PCI patients who are treated at both institutions. We have incorporated a 29% oversample of women to ensure a sufficient sample size to examine subgroup differences in intervention effects, given the low enrollment of female Veterans in Veterans Health Administration (6%) [38]. Inclusion criteria include: (1) >21 years of age, (2) recent ACS or PCI within one week, and (3) new antiplatelet (thienopyridine) prescription. Exclusion criteria are: (1) cognitive impairment, and (2) lack of English proficiency/literacy. For the process evaluation, we will recruit a subset of 10 participants from each experimental group (text messaging and mobile app; total n=20) for in-depth individual interviews.

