#### Baseline Data Collection

After written consent is obtained, we will collect clinical data by reviewing electronic medical records. Participants will complete the following baseline questionnaires: (1) sociodemographic information and medical history, (2) mobile phone use, and (3) Mini-Cog Test [39]. All instruments and frequency of administration are described in Table 2.

**Table 2 table2:** Measurement of medication adherence with intervals.

Measure	Description	Rationale	Months					
			0	1	3	6	9	12
Key Primary Endpoint								
Medication Event Monitoring System (MEMS) [40]	Electronic pill caps time stamp when the bottle is opened, correlating with intake of medication. Primary outcome is percentage (0-100%) of prescribed doses taken	Most objective, noninvasive method and considered the “gold standard”		x		x		x
Secondary Patient-Reported Endpoints								
MEMS [40]	Percentages (0-100%) of (1) days correct doses are taken, and (2) doses taken on schedule	Most objective, noninvasive method and considered the “gold standard”		x		x		x
Morisky Scale [41,42]	Eight-item Morisky Medication Adherence Scale (MMAS-8) self-reported questionnaire on adherence behavior for a range of scores 0-8, with higher scores indicating poor adherence (Cronbach alpha=0.83).	Most popular scale and well-validated instrument with high reliability	x	x		x		x
7-Day Recall	One item asking how many days in the past week patient remembered to take medications. Final outcome is a percentage (0-100%).	Most commonly used method in the clinical setting	x	x		x		x
Secondary Objective Endpoints								
Veterans Affairs Corporate Data Warehouse (Veterans)	Veterans Affairs software program that provides detailed information on inpatient and outpatient medications. Final outcome is a percentage (0-100%) of days covered during 90-day period.	Assesses adherence via 90-day refill patterns (does not require active participation)		x	x	x	x	x
Peoplechart Meds Incontext (non-Veterans)	Private software program that uses refill data directly from retail pharmacies and Personal Benefits Manager. Final outcome is a percentage (0-100%) of days covered during 90-day period.	Assesses adherence via monthly refill patterns (does not require active participation)		x	x	x	x	x

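### The primary test is a group-by-time interaction with no MEMS baseline, so a benefit present from month 1 and sustained would not be detected

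*Protocol article*

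**What the plan says.** Four parts of the protocol article bear on the primary comparison of Aim 3.

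- **Outcome** (Analysis, Medication Adherence): "The primary outcome will be the percentage of prescribed doses taken based on MEMS data (aggregated over 12 months"). This is one percentage per patient.
- **Model and primary parameters** (Primary Statistical Analysis): "The predictors will be a categorical predictor of group (with control as reference), time, and the group-by-time interactions", plus recruitment site. Then: "The parameters in the group-by-time interaction are the primary parameters of interest, describing whether adherence changes differentially over baseline". Neither the group term nor an average group difference is named as primary.
- **Measurement times** (Baseline Data Collection, Table 2): the key endpoint row reads "Primary outcome is percentage (0-100%) of prescribed doses taken" and is marked at months 1, 6 and 12. The MMAS-8 and 7-day recall rows are marked at month 0 and the MEMS rows are not. Follow-Up Visits agrees: "Subsequent in-person follow-up visits at 1, 6, and 12 months will take place". The inclusion criteria in Sample require "2) recent ACS or PCI within one week, and (3) new antiplatelet (thienopyridine) prescription", so patients have no earlier period on the drug to record.
- **Power** (Sample Size Estimation): 225 enrolled, 15% attrition, 192 analysed, and 86% power for a half-SD difference between at least one intervention group and control by Dunnett's method.

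**The concern.** A single aggregate per patient cannot have a group-by-time interaction, and a change over baseline needs a baseline that is not scheduled for this measure. If the model is fitted to the three MEMS values that are scheduled, every value is post-intervention. The interaction then describes only how the gap between arms changes after month 1. A benefit that is fully present at month 1 and lasts all year goes into the group term, which is not primary.

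This time course is plausible. The sponsor's pilot lasted 30 days, and in it "electronic devices revealed that patients who received text messaging for antiplatelets had a higher percentage of correct doses taken". The pilot reported a 15% to 17% gain, and Sample Size Estimation cites its d = 0.69. An effect that appears within 30 days is already there at the first MEMS time point.

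Two wrong readings could follow. An effective, sustained intervention would give a null primary result. One that starts strongly and partly wanes could give a significant negative primary result although adherence is higher at every visit.

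**Working it through.** **Inputs.** From the article: 64 per arm (192/3; 225 × 0.85 = 191.25), MEMS at months 1, 6 and 12, d = 0.5 and 0.69, Dunnett adjustment. Assumed because not stated: two-sided 5% familywise alpha, equal SD (set to 1) at each visit, a random intercept giving a common within-patient correlation ρ of 0.3 to 0.7, and complete data. The Dunnett critical value (3 arms, 189 df) is 2.227.

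**1. The plan's own figure.** For a single difference in means, the standard error is √(2/64) = 0.1768, so z = 0.5/0.1768 = 2.83. Power per comparison is about 0.73. The probability of at least one rejection with both arms effective is 0.862, which reproduces the stated 86%. For d = 0.69 the same calculation gives 0.989 (0.957 if only one arm works), consistent with the stated figure of more than 95%. The stated power is therefore for a difference in levels.

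**2. The named primary parameters, constant effect.** Mean time is 19/3 = 6.33 months, and Sxx = 5.33² + 0.33² + 5.67² = 60.67. The SE of a difference in slopes is √[(1−ρ)/60.67 × 2/64]. A constant effect gives a slope difference of exactly 0, so rejection is 1.3% per tail, 2.6% per comparison and about 4.8% for either comparison, whatever ρ and whatever the size of the benefit.

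**3. A test of level on the same data.** Equal weights over visits: SE = √[(1+2ρ)/3 × 2/64]. For d = 0.5, z = 3.87, 3.46 and 3.16 at ρ = 0.3, 0.5 and 0.7, giving power per comparison of 95%, 89% and 82%. Weighting by interval length (1, 5 and 6 months) gives 92%, 87% and 81% per comparison, and 98%, 95% and 92% for at least one rejection.

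**4. Simulation.** In 400 simulated trials at ρ = 0.5, with a mixed model containing group, time, interaction and site, the interaction rejected at least once in 4.75%. A linear model on the interval-weighted aggregate did so in 93.5%.

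**5. Waning effect of 0.69, 0.50, 0.30 SD.** Slope difference = (−5.33×0.69 − 0.33×0.50 + 5.67×0.30)/60.67 = −0.0354 SD per month. z = −1.86, −2.20 and −2.85 at ρ = 0.3, 0.5 and 0.7. The probability of a significant negative interaction per comparison is 36%, 49% and 73%.

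**6. Summary by time course** (at least one rejection, both arms effective; ρ = 0.3 / 0.5 / 0.7):

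| Effect at months 1, 6, 12 (SD) | Interaction | 12-month weighted level |
|---|---|---|
| 0.5, 0.5, 0.5 | 0.05 / 0.05 / 0.05 | 0.98 / 0.95 / 0.92 |
| 0.25, 0.5, 0.5 | 0.23 / 0.31 / 0.47 | 0.97 / 0.93 / 0.90 |
| linear from 0 at month 0 to 0.5 at month 12 | 0.66 / 0.80 / 0.95 | 0.80 / 0.73 / 0.66 |
| 0.69, 0.50, 0.30 | 0.51 / 0.66 / 0.87 (essentially all negative) | 0.91 / 0.85 / 0.80 |

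**The case against.** The strongest reply is that a trajectory is a legitimate target. The Introduction and Abstract describe nonadherence that accumulates: one in seven MI patients with drug-eluting stents off antiplatelets at 30 days, and 21% to 57% nonadherent by 12 months. If the intervention slows that decline, the interaction can detect it, and for linear growth it is the stronger test at ρ of 0.5 and above. That stands. The failure is confined to effects that come early and then hold or wane. It still leaves the primary result depending on the shape of the effect rather than on whether adherence improved, which is the stated objective.

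The group term is fitted in the same model, so a constant benefit would be estimated. That is true, but it is not a primary parameter. With linear time counted from month 0, its coefficient is also an extrapolation to month 0 rather than a 12-month average.

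The option of arbitrary means chosen by AIC/BIC does not help: with month 1 as the earliest value, a constant effect still gives zero interaction. MEMS time-stamps every opening, so finer intervals are possible, but all would still fall after the intervention starts.

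Some figures depend on choices made here. The waning profile is illustrative; only 0.69 is in the article, and it comes from a pilot with a no-message control rather than a website. A milder decline (0.69, 0.55, 0.50) gives a significant negative interaction in about 9% to 19%. Taking 0.5 SD on the SD of the aggregate itself, rather than per visit, lowers the level test to the article's own 86% (about 73% per comparison). None of this changes the constant-effect result.

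**Conclusion.** The concern holds. The outcome definition and the power calculation both point to a between-arm difference in level over 12 months. The analysis section instead makes primary an interaction relative to a MEMS baseline that is not scheduled. For a benefit present at month 1 and sustained, the named primary parameters have no power beyond the type I error rate (about 5% for either comparison), against 86% on the article's own scale or 92% to 98% with 0.5 SD taken per visit. The null result under a constant effect does not depend on the correlation or on the effect size. The 92% to 98% and the 36% to 73% for the waning profile rest on the assumed correlations of 0.3 to 0.7, equal visit SDs, two-sided 5% familywise alpha and complete data. The claim concerns the named primary parameters; an effect that grows over the year could be detected by them.

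**What to change.** In Primary Statistical Analysis, name as primary the two between-arm differences (text messaging versus website, app versus website) in percentage of prescribed doses taken over 12 months, adjusted for site and tested with the Dunnett adjustment already set in Sample Size Estimation. Either of these would serve, and one should be fixed in advance:

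- a linear model with group and site on the 12-month aggregate; or
- a mixed model with categorical interval (0–1, 1–6, 6–12 months), with the interval-length-weighted average group contrast as the primary parameter.

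Remove the reference to change over baseline for MEMS. It can stay for MMAS-8 and 7-day recall, which have month-0 values. Keep group-by-time as a secondary question about durability. The cost is a wording change before enrolment, with no extra patients or data, and the existing power statement then applies to the test that is done.

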#### Sample Size Estimation

We plan to enroll 225 total participants (75 participants per group). Allowing for a 15% attrition rate over the 12-month study, we conservatively estimate that this recruitment target will result in a total sample size of n=192, which will give 86% power to detect a medium effect size (half-SD difference) between at least one treatment group and the control group using Dunnett’s method to adjust for multiple comparisons. This sample size would give more than 95% power to detect an effect size of d=0.69, as found in our previous clinical trial [33]. Analysis of the longitudinal data points with mixed-effects models will confer additional power.

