#### Randomization

Group assignment will be generated by random allocation sequence using random blocks stratified within recruitment site (SFVAMC or JMMC) of either three or six, which will be prepared by the study biostatistician. The research team will assign patients to their groups by distributing presealed envelopes in consecutive, numbered order. Due to the nature of the study design, the research team and participants cannot be blinded to the intervention once group assignment is determined.

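### The time function, and with it the primary interaction contrasts, is left to AIC/BIC, and the Dunnett adjustment behind the power figure is not tied to those contrasts

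*Protocol article*

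**What the plan says.** Four sections of the protocol article (Aim 3) bear on the point.

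- **Primary Statistical Analysis.** The base model is a linear mixed model with group (control as reference), time, group-by-time and recruitment site. The interaction parameters are declared primary. The same paragraph continues: "We will also investigate whether other models for change over time are more appropriate, including arbitrary means or nonlinear time functions", using AIC/BIC. Secondary analyses are named only in the sentence after that. The paragraph mentions no multiplicity adjustment.
- **Sample Size Estimation.** The 86% power is for a half-SD difference between control and at least one active arm, "using Dunnett’s method to adjust for multiple comparisons". Attrition enters as "Allowing for a 15% attrition rate over the 12-month study", and "this recruitment target will result in a total sample size of n=192".
- **Medication Adherence (analysis).** The primary outcome is one MEMS percentage per patient, aggregated over the year. Table 2 schedules MEMS at months 1, 6 and 12, with no month-0 value.
- **Randomization.** The trial is open-label: "the research team and participants cannot be blinded to the intervention once group assignment is determined".

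**The concern.** An interaction coefficient has no meaning apart from the time function it multiplies. Under linear time it is a difference in slope per month; under log time it is something else; under arbitrary means it becomes two differences per arm. If model fit decides among these, the null hypothesis and the number of primary tests are settled by the outcome data. No rule says when an alternative displaces the base model, or what happens if AIC and BIC disagree.

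Two things are at stake. The first is error control: a search among models that contain group-by-time terms tends to favour the form in which the arms happen to diverge, and a Dunnett critical value for two comparisons does not allow for that. The second is the power statement: it was computed for two Dunnett-adjusted mean differences, and the paragraph that defines the primary test names neither the adjustment nor a mean difference.

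**Working it through.** **Inputs.** Stated: 225 randomised equally to three arms, 15% attrition, 192 analysed, effect 0.5 SD, MEMS at months 1, 6 and 12. Assumed because not stated: two-sided family-wise 5%, within-patient correlation 0.5-0.6, normal errors, random intercept, candidate time functions linear, log and categorical.

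**Step 1. Reproduce the stated power.** 225 × 0.85 = 191.25, stated as 192, so 64 per arm. The noncentrality for one comparison is 0.5 × √(64/2) = 2.83. The two-sided 5% Dunnett critical value (two comparisons, 189 df) is 2.227.

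- At least one comparison significant, both active arms at 0.5 SD: 86.1%, matching the stated 86%.
- Variants: one given comparison 72.6%; unadjusted 91.4%; one-sided 92.2%; Bonferroni 85.4%.

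Two-sided 5% with Dunnett on two mean differences is therefore a sound reading of what was powered, although Bonferroni comes close.

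**Step 2. Count the primary parameters.** With three arms and a time function of p parameters there are (3 − 1) × p interaction coefficients: 2 when p = 1, and 4 for arbitrary means at three visits (p = 2).

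**Step 3. Family-wise error without adjustment.** Two equal-sized arms compared with a shared control give test statistics with correlation 0.5. At 5% each, 1 − P(|Z1| < 1.96 and |Z2| < 1.96) = 9.1%; treated as independent, 1 − 0.95² = 9.75%. The other figures come from simulated null trials with 64 per arm at months 1, 6 and 12, 8,000 per scenario and correlation 0.6, over several common time courses.

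| Rule, no adjustment | Family-wise error |
|---|---|
| Two coefficients, time function fixed | 9.1% |
| Time function chosen by BIC | 9.5-10.6% |
| Time function chosen by AIC | 12.4-15.1% |
| Four coefficients, any one counts | 16.0% |

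**Step 4. Family-wise error with Dunnett kept.** The simulation error near 5% is about √(0.05 × 0.95/8,000) = 0.24 percentage points.

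| Rule, Dunnett-type adjustment | Family-wise error |
|---|---|
| Linear time fixed in advance | 4.5-5.0% |
| Form chosen on pooled data, no group-by-time terms (correlation 0.5) | 4.7-5.3% |
| BIC, candidates with group-by-time terms (correlation 0.5) | 5.4-6.5% |
| AIC, critical value covering all coefficients of the chosen model (correlation 0.5-0.6) | 5.9-7.4% |
| AIC, two-contrast critical value throughout (correlation 0.6) | 7.8-8.8% |

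A separate AIC run at correlation 0.5 gave 6.5-8%, inside the span of the last two rows. For four coefficients, the critical value that holds 5% is about 2.46, against 2.227 for two.

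**Step 5. Compare what was powered with what is tested.** Step 1 describes a difference in means between arms, which fits an outcome aggregated over 12 months. The primary analysis tests differential change over time. The 86% therefore does not describe the test that the analysis section calls primary, whichever time function is chosen.

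**The case against.** The strongest defence has three parts.

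1. **The adjustment is named.** The protocol names Dunnett, and the stated power reproduces with it. Attaching it to particular coefficients is something an article may leave to an analysis plan that is not shown. This stands. A reader might infer that the trial's family-wise error is 9-16%, but that requires Dunnett to be dropped, and silence in one paragraph does not show that. The 16% further requires that any one of four coefficients counts as success. The text asks about each active arm against control, which one joint test or one contrast per arm would answer equally well.
2. **Unblinded selection is not stated.** A reader might infer that the time function is chosen with treatment labels visible. The Randomization section covers the research team and participants; it does not say how the model comparison is made. If the form is chosen on pooled data without group-by-time terms, the inflation disappears (4.7-5.3%).
3. **The sentence may be exploratory.** It can be read as an addition to a base model that stays primary. That reading is possible. Against it, the sentence stands under the primary-analysis heading, before secondary analyses are introduced, and speaks of other models being more appropriate. That suggests replacement rather than a sensitivity check.

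The first two parts limit the size of the problem; the third leaves the sentence's status open. None of them fixes which contrasts are primary.

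**Conclusion.** The point holds in limited form. As written, the primary contrasts are not fixed: outcome-based model fit may change their meaning and their number (two or four), and the adjustment used for power is not linked to them. On the reading most favourable to the sponsor, with Dunnett kept, family-wise error runs from about 5% to about 9%. It stays near 5% if the form is chosen on pooled data, is slightly above with BIC, and is highest with AIC on models containing group-by-time terms. The 9-16% range is conditional on unadjusted testing and is not the trial's established error rate.

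The 5% benchmark is itself assumed, though it reproduces the 86%. The selection figures depend on the assumed correlation and candidate functions, so their exact size is uncertain. That the test is left open does not depend on them. This should be corrected before outcome data are examined.

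**What to change.** Rewrite the primary-analysis paragraph to do four things.

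1. Pre-specify categorical time (months 1, 6, 12) as the primary mean model. With three scheduled visits it is saturated in the means, so no search for a time function is needed.
2. Name exactly one contrast per active arm against control. Categorical time alone is not enough, since it leaves four interaction coefficients. The mean over the 12 months is a natural example: it matches both the aggregated outcome and the mean difference that was powered, and it needs no month-0 MEMS value. State the weights. With month 1 as reference, group effect g and interactions d6 and d12, equal weights give g + (d6 + d12)/3. If each reading covers the time since the previous visit (1, 5 and 6 months), interval weights give g + (5·d6 + 6·d12)/12.
3. State alpha, and test these two contrasts with Dunnett at family-wise 5%.
4. Label the AIC/BIC trajectory modelling as secondary.

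The cost is one paragraph of text. Against linear time the model gains 3 × 3 − 3 × 2 = 3 mean parameters, negligible with 192 patients. The real trade-off is that the shape of the adherence trajectory becomes a secondary question.
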